### Secondary outcomes

#### Individual LIBRA2 factors

Measures of all individual factors of the LIBRA2 are included as separate secondary outcomes. These include questionnaires on mediterranean diet (Mediterranean Diet Adherence Screener; MEDAS) [37], physical activity (European Prospective Investigation into Cancer and Nutrition; EPIC) [38], cognitive activity (Cognitive and Leisure Activities Scale) [39], depression (PHQ-9) [40] and stress (Perceived Stress Scale) [41], sleep quality (GSKS) [42], social participation (Lubben social network scale) [43] and loneliness (De Jong Gierveld 6-item Scale) [44]. Questionnaires have been validated and used in previous Dutch studies [35, 45]. Participants complete these questionnaires online at home (via Castor EDC). If this is not feasible, participants are provided the opportunity to complete the questionnaires on paper. Smoking and alcohol use (including duration and quantity) and diagnosis of health conditions (hypertension, hypercholesterolemia, coronary heart disease, diabetes, kidney disease, depression, sleep disorders) are assessed through self-report.

Objective measures to define obesity and hypertension include height, weight, and blood pressure (average of three measures while sitting). Lab measures are used to objectively define hypercholesterolemia (through total cholesterol, LDL cholesterol, HDL cholesterol, and triglyceride levels), diabetes (through HbA1c levels), and kidney disease (through creatinine/eGFR levels). These are determined in the blood by standard local protocols (5 ml serum for HbA1c, 4 ml heparin for creatinine and lipids). The presence of health conditions is operationalized through either the presence of a self-reported diagnosis or abnormal values of objective measures, using the same cut-offs as used for calculating LIBRA2 (Table 2).

#### Cognitive functioning

Cognition will be assessed with neuropsychological assessment [46] across different cognitive domains: short- and long-term memory (15-Word Verbal Learning Test) [47], working memory (Wechsler Adult Intelligent Scale digit span) [48], attention (Trail Making Test A), executive functions (Trail Making Test B) [49], information processing speed (Digit Symbol Substitution Test) [50] and language (semantic word fluency, category animals) [51]. At follow-up, parallel tests will be performed for the 15-Word Verbal Learning Test and semantic fluency (category professions). Cognitive testing will be performed according to standard local guidelines of the memory clinic. Tests will be performed and scored by researchers trained in neuropsychological testing and z-scores will be calculated to standardize the scores using local norms. Conversion to MCI or dementia during the study will also be collected if available (based on clinical diagnosis). At follow-up, measures of cognitive functioning are collected by researchers blinded to the intervention group.

#### Daily functioning, psychological and knowledge outcomes

To what extent participants have difficulties in everyday functioning is measured with Amsterdam Instrumental Activities of Daily Living Questionnaire (A-IADL-Q) [52]. Psychological outcomes include locus of control (Health locus of Control Scale) [53], self-efficacy (General Self-Efficacy scale) [54], and mastery (Pearlin Mastery Scale) [55]. In addition, knowledge on dementia risk is assessed (Knowledge on dementia risk questionnaire). Questionnaires have been validated and used in previous Dutch studies [35, 56].

#### Process evaluation

To identify barriers, and facilitators and evaluate strategies for sustainable implementation of the lifestyle intervention in this study, we perform a mixed-method process evaluation. Based on the UK Medical Research Council guidance on process evaluation of complex interventions [57], we collect data on implementation, mechanisms of impact and context. Implementation includes reach (proportion of eligible members of the target group that participated in the intervention), recruitment (sources and procedures for recruitment and reasons for joining or not), fidelity (the extent to which the intervention was delivered as intended), dose delivered (how much of the intervention was provided) and dose received (how much of the delivered intervention was assimilated by participants who were engaged). Mechanisms of impact covers experiences and usefulness of the intervention. Context includes external characteristics of stakeholders and facilitating factors and barriers to delivery of the intervention. Table 3 provides a detailed summary of the process evaluation objectives and methods employed, organized by the domains of implementation, mechanisms of impact and context according to the MRC framework for each stakeholder. Stakeholders in the process evaluation are patients, lifestyle coaches and healthcare professionals (e.g. neurologist, research nurse, general practitioners and community-based lifestyle initiatives). Data will be gathered at different time points throughout the intervention from different stakeholder groups by means of questionnaires, interviews and/or focus groups. Patients will receive three questionnaires throughout one year; lifestyle coaches and other healthcare professionals will receive one questionnaire once randomization is completed. For the post-intervention interviews and/or focus groups with patients, a subset will be selected using purposeful sampling based on sociodemographic factors aiming to include 12–20 participants (3–5 per arm per site) representative of the memory clinic population. All lifestyle coaches and healthcare professionals are invited to participated in a semi-structured interview. Other data registration consists of field notes from conversations, phone calls, meetings, email and measurement observations from our researcher with patients and healthcare professionals (e.g. electronic health record or case report forms and other databases). Also, patients’ usage of BreinZorg is automatically registered. Lifestyle coaches keep pre-structured logs of coach-sessions with the patients. The extent to which lifestyle coaches deliver the intervention according to motivational interviewing guidelines will be assessed using the Motivational Interviewing Treatment Integrity (MITI 4.2.1) scale [58]. We aim to code at least four sessions with different patients of each lifestyle coach (weighed for total number of patients counselled) to provide a reliable competency score for fidelity across the trial.

**Table 3 Tab3:** Overview of the process evaluation objectives and methods in the different stakeholder groups

Stakeholder Method Timepoint Domain	Patients (both arms)				Lifestyle coach			Healthcare professional		
	Questionnaire			Interview	Questionnaire	Interview	Data registration	Questionnaire	Interview	Data registration
	T = 0	T = 3	T = 12	T = 12^*^	Randomization completed	T = 12	Continuous	Randomization completed	T = 12	Continuous
Implementation										
Reach							field notes			field notes
Recruitment	x			x				x	x	
Fidelity					x	x	audio recording, field notes	x	x	field notes
Dose delivered					x	x	pre-structured logs			
Dose received		x	x	x			field notes, BreinZorg	x	x	field notes
Mechanisms of impact										
Experiences and usefulness		x	x	x	x	x		x	x	
Context										
Characteristics					x			x		
Facilitators and barriers			x	x	x	x		x	x	

Domains are based on UK Medical Research Council guidance on process evaluation of complex interventions. Field notes are documentations in electronic health record or case report forms and/or other databases on conversations, phone calls, meetings, email and measurement observations with patients and healthcare professionals

*Subset *N* = 12–20 (3–5 participants per arm per site)

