So far, most research comes from studies in the general population, while evidence for indicated prevention in memory clinics (in stages of subjective cognitive decline (SCD) and mild cognitive impairment (MCI)), is lagging behind. These patients generally have worse health and lifestyle profiles and are at higher risk for dementia [17, 18]. While they might, thus, benefit from preventive measures, there are currently no integrated preventive measures for dementia risk reduction in routine clinical care [19]. Real-world implementation of interventions studied in earlier WW-FINGER trials is difficult due to strict programs and high intensity [20]. Therefore, it is necessary to explore more personalised intervention options and to assess their implementability in healthcare.

Therefore, the primary objectives of the Lifestyle Intervention at General and academic Hospitals Trial (LIGHT) are to: (1) test the effectiveness of a lifestyle intervention on improving the dementia risk profile of people with SCD and MCI in a randomized controlled trial (RCT), as compared to general health advice (2) identify barriers, facilitators and evaluate strategies for sustainable implementation of the lifestyle intervention, and (3) estimate the cost-effectiveness of the lifestyle intervention from a lifetime horizon and societal perspective.

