## Methods

### Study design

LIGHT is a multi-center RCT assessing the (cost-)effectiveness of a 1-year personalized lifestyle intervention as compared to usual healthcare and general health advice with 300 participants. Participating research centers include Maastricht University and Amsterdam University Medical Center. Outcome measurements are conducted at baseline and at the end of the 1-year intervention. LIGHT has been approved by the medical ethical committee of MUMC+ (NL86513.068.24) and is registered at Dutch trial register OMON (NL-OMON57198) and ClinicalTrials.gov (NCT06832761, registration date February 18th 2025). This study will be conducted in accordance with the ethical conduct and juridical laws of the Declaration of Helsinki (2013), Good Clinical Practice (GCP) as defined by the International Conference on Harmonization (ICH) Guidelines, and the Medical Research Involving Human Subjects Act (WMO). Results will be reported in line with the Consolidated Standards Of Reporting Trials (CONSORT) guidelines [21].

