#### Adherence

Additionally, adherence measures will be recorded to track real-world feasibility and implementation. Adherence measures include the number of appointments with the lifestyle coach or research visits missed, the number of personal goals set and reached, the number of vouchers provided and their usage, and a usage log of BreinZorg (login times, completion of learning modules).

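### The patient-interview sampling rule does not secure any low-adherent or withdrawn intervention patient, so the in-depth account of barriers may lean towards completers

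*Protocol article*

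**What the plan says.** The Background lists, as the second primary objective, to "identify barriers, facilitators and evaluate strategies for sustainable implementation of the lifestyle intervention".

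The Process evaluation section sets out how patients are chosen for interview. It states that "a subset will be selected using purposeful sampling based on sociodemographic factors". The interviews or focus groups take place after the intervention, and the target is 12–20 patients, 3–5 from each arm at each site, who should reflect the clinic population. Table 3 repeats the size of the subset, places the interviews at T = 12 and covers both arms. In its row on facilitators and barriers, patients are marked only at T = 12, for the questionnaire and the interview. The T = 3 patient questionnaire is marked for dose received and for experiences and usefulness, but not for barriers.

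The Adherence section records missed coach appointments and research visits, goals set and reached, "the number of vouchers provided and their usage, and a usage log of BreinZorg". None of these is named as a basis for choosing interviewees. The Control group section gives controls a binder with general advice and lists no coach, vouchers or platform.

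**The concern.** Patients who miss sessions, leave vouchers unused or stop early know most directly what stood in the way of the intervention. The stated rule diversifies interviewees on sociodemographic factors but contains nothing that brings these patients in. Interviewing at month 12 makes it more likely that they are out of reach by then.

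The plan itself expects adherence to matter. The Background offers adherence problems as a possible reason why earlier trials found no effect on cognition, and the Effectiveness analysis section plans a per-protocol analysis without low adherers. If the interviews under-represent these patients, the patient view of what hinders the intervention could look too favourable. That view also carries forward, because the Cost-effectiveness analysis section takes inputs for the budget impact analysis partly from the process evaluation.

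**Working it through.** **Inputs**
- 3–5 interviewees per arm per site, 12–20 in total (Process evaluation; Table 3).
- Two arms, 1:1 (Randomization and blinding).
- Two sites: "Participating research centers include Maastricht University and Amsterdam University Medical Center" (Study design).
- 10% dropout (Sample size).
- Proportion of low adherers: not given. Assumed here to be 20% to 40%.

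**1. Reproducing the plan's figure.** Interviews = patients per arm per site × arms × sites. 3 × 2 × 2 = 12 and 5 × 2 × 2 = 20, which matches the stated 12–20.

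**2. Interviewees exposed to the intervention.** 3 × 2 = 6 and 5 × 2 = 10. The other half are controls, who cannot describe barriers to using the coach, vouchers or platform.

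**3. Chance that no dropout is interviewed.** If selection is unrelated to dropout, P(none) = (1 − d)^n.
- d = 0.10, n = 6: 0.9^6 = 0.53; expected number 6 × 0.10 = 0.6.
- d = 0.10, n = 10: 0.9^10 = 0.35; expected number 10 × 0.10 = 1.0.

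**4. Chance that no low adherer is interviewed**, by the same formula and on assumed rates:

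| Assumed share of low adherers | n = 6 | n = 10 |
|---|---|---|
| 20% | 0.8^6 = 0.26 | 0.8^10 = 0.11 |
| 30% | 0.7^6 = 0.12 | 0.7^10 = 0.03 |
| 40% | 0.6^6 = 0.05 | 0.6^10 = 0.006 |

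At 20%, the chance of at least one low adherer is 1 − 0.26 = 0.74 to 1 − 0.11 = 0.89. A neutral selection would usually include some low adherers but could easily include no dropout.

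**5. Other patient sources in Table 3.** The T = 12 questionnaire is not limited to the interview subset and does ask about barriers, but a patient who left earlier and is not reached at month 12 will not answer it. The T = 3 questionnaire reaches patients earlier but is not marked for barriers. Coach logs and platform logs show that use stopped; they are not the patient's own account of why.

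**The case against.** The strongest counter-argument is that the interviews are one source among many. Barriers are also covered by the T = 12 questionnaire, by the coach and professional questionnaires, and by interviews to which all coaches and professionals are invited. Session logs, field notes and automatic platform logs run throughout. Sociodemographic sampling fits the trial's rationale, since the Discussion names socio-economic status and access to resources as barriers to behaviour change. Nothing in the text excludes low adherers or dropouts from interview. Purposive selection is not random drawing, so the probabilities are only a yardstick, and the 10% is trial dropout, not non-adherence.

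Most of this stands and limits the point. A reader might infer that objective 2 will be answered almost entirely by adherent completers. The documents do not support that: the other sources are substantial, no rule restricts interviews to completers, and some low adherers would usually be included.

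A reader might also object that "lifestyle coaches and other healthcare professionals will receive one questionnaire once randomization is completed", before the last patients have had their later sessions. Table 3 largely answers this with coach and professional interviews at T = 12 and continuous logging. Nor is interviewing controls an error: Table 3 covers both arms and includes recruitment, on which controls can speak.

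The objection does not remove the gap in patients' own in-depth accounts. The article is condensed, but it states the sampling basis explicitly, so this is a stated choice and not detail left to a fuller document.

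**Conclusion.** The point holds in a limited form. The sampling rule does not ensure that any low-adherent or withdrawn intervention patient is interviewed, and patients are scheduled to be asked about barriers only at month 12. With 6–10 exposed interviewees and 10% dropout, the chance of interviewing no dropout is about 0.35 to 0.53. This assumes that selection is unrelated to dropout and that dropouts are as reachable at month 12 as completers; if they are harder to reach, the chance is higher. The figures for low adherers rest on assumed rates. The consequence is a possible lean towards completers in one source for objective 2, partly offset by the others. The primary outcome and the effectiveness analysis are not affected.

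**What to change.** Keep the 12–20 interviews and the allocation per arm and site. In the intervention arm, name recorded adherence or withdrawal status (sessions attended, vouchers used, BreinZorg log) as a purposive sampling dimension beside sociodemographic factors. Aim for at least one low-adherent or withdrawn intervention patient per site. Approach patients who stop early at the time of withdrawal, if they agree, without waiting for month 12.

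The change is to the wording of the sampling frame, uses data already collected and adds no interviews. The downside is that such patients are harder to recruit, so the per-site aim should be a target and not a requirement, with any shortfall reported.

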#### Cost-effectiveness

In an early health-technology assessment, the cost-effectiveness of the lifestyle intervention will be estimated from a societal perspective (reflecting medical sector, social sector, patient and family, and productivity loss) over a lifetime horizon. Measures involve health related quality of life (EuroQol-5D-5 L) [59], capability (ICEpop CAPability measure for Older people, ICECAP-O) [60]. In addition, questionnaires for care use (Medical Consumption Questionnaire) [61] and productivity (Productivity Costs Questionnaire) [62] are performed.

#### Adherence

Additionally, adherence measures will be recorded to track real-world feasibility and implementation. Adherence measures include the number of appointments with the lifestyle coach or research visits missed, the number of personal goals set and reached, the number of vouchers provided and their usage, and a usage log of BreinZorg (login times, completion of learning modules).

#### Other measures

Demographical data (age, sex, education, household income, work, ethnicity, marital status, living condition) will be collected. Participants are additionally asked whether they are already following any lifestyle-related treatment, for example by a dietician or cardiovascular management at the general practitioner. As part of the lab measures, additional blood is drawn (6 ml) and stored in the biobank for determining APOE genotype (if not already available) and biomarkers (e.g. amyloid and p-tau) in the future.

### Sample size

For power calculation, we used mean scores of the primary outcome, the LIBRA2 score, in people with SCD and MCI as reported in a previous study [31]. A 1-point difference in LIBRA2 scores between the intervention and control group at the end of the study would translate into a Cohen’s d = 0.35. To detect such a small to moderate effect size with 80% power in two-sided testing at an alpha-level of 0.05 and a 1:1 treatment allocation ratio, 133 patients per group are needed. Further assuming a 10% dropout rate during the trial means that we need 148 participants per group, resulting in a total sample size of 296, which was rounded up to 300.

### Data analysis

Demographics will be described and compared between centers and diagnostic status by using t-tests (continuous data) and chi-squared tests (categorical data). Assumptions will be checked, and transformations will be used where necessary.

#### Effectiveness analysis

We will use linear mixed model analyses to test the effect of the intervention on the primary and secondary outcome variables (except secondary measures collected for process evaluation and cost-effectiveness) as these models generally handle missing outcome data well and thereby align with the intention-to-treat principle, even if only baseline values are available [63]. Models will use a random intercept (individuals) and, if likelihood ratio testing suggests better fit, random slopes (time). Treatment group (intervention or control) and time (baseline and 1-year follow-up) will be included as fixed effects, and study site and diagnostic group (SCD or MCI) as fixed covariates. Additional covariates will be added if randomization was not successful in balancing other characteristics (e.g. age, gender and education) between treatment groups. An interaction term between treatment group and time will be included as fixed effect. The intention-to-treat principle is used by including all randomized participants in the analyses, including dropouts and non-adherent participants. Missing primary and secondary outcome data are considered as missing-at-random (i.e., missingness is probabilistic and conditional on the covariates included in the analyses) and handled efficiently through maximum likelihood estimation of expected scores in the linear mixed model [64]. We will additionally assess differences in effectiveness and adherence between the SCD and MCI groups using stratified analysis. All analyses will be two-sided at an alpha level of 0.05 and conducted in Stata 18 or higher. A per-protocol sensitivity analysis will be performed to assess whether results remain consistent when excluding participants with low adherence to the intervention.

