### Randomization and blinding

After the baseline visit, participants are randomized with a 1:1 ratio to either the intervention group or control group. Block randomization (in variable groups of two and four) stratified for study centre and diagnosis (SCD or MCI) is used. Randomization is done by a computer-generated allocation scheme integrated in the Castor electronic data capturing system (Castor EDC, Amsterdam, The Netherlands). Researchers executing cognitive assessments at follow-up are blinded for group allocation. Group allocation is not actively disclosed to participants, but complete blinding is unlikely due to the nature of the intervention.

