### Personalized lifestyle intervention

An overview of the study design is shown in Fig. 1. The personalized lifestyle intervention includes three components:

Lifestyle coach

The first and main component of the intervention involves three personal sessions with a certified lifestyle coach. At the start of the intervention (2–4 weeks after the baseline assessment), the coach will provide tailored advice (on site or through an online video call). The coach discusses the individual lifestyle risk profile (based on baseline LIBRA2 measures, see below) and through motivational interviewing [26], suggests lifestyle changes based on the risk factors with suggested room for improvement. The participant and lifestyle coach agree on an individual plan and set realistic personal goals, also considering the personal aims and wishes of the participant. Tailored advice may for example comprise specific advice on how to be more physically active or to adopt more healthy dietary choices based on the participants’ personal preference and motivation. Participants may be referred to suitable professional help (e.g. dietician, stop smoking program) or community-based lifestyle initiatives (e.g. free sports initiatives for elderly, cooking groups) to facilitate and maintain behavioural change. Two follow-up sessions 3 and 9 months after the first visit are intended to discuss progress and, if needed, adjust or set new personal goals. Sessions will take 1 to 1.5 h.

2.Voucher program

The second component is a voucher program, which was co-developed with regional partners, to support participants in making a first step towards a brain-healthy lifestyle. The voucher program is inspired by a similar program that is implemented in the Programme Dementia Prevention (pdp) in Luxembourg [27]. Participants receive up to two vouchers from the lifestyle coach per visit (with a total of six vouchers, each worth 50 euros) to support brain healthy behaviours tailored to the individual risk profile and goals as discussed with the lifestyle coach. These vouchers provide access to services across multiple domains: physical activity, social participation, cognitive activity, and healthy diet and include, among others, gym memberships, free entrance to museums, or fresh vegetable and fruit from local farmers. The lifestyle coach has an advisory and motivational role in the voucher usage.

3.Access to online platform

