### Control group

The control group receives general health advice through a similar binder, including the same general information about the LIBRA2 factors in relation to brain health and dementia. Participants in both groups will receive regular online newsletters and updates as well as gift vouchers (75 euros in total) for their participation.

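### Only the intervention arm is nested within lifestyle coaches, yet the stated model has no coach term, so its standard error can be too small if coaches differ

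*Protocol article*

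**What the plan says.** The section on randomization and blinding makes the individual the unit of allocation: "participants are randomized with a 1:1 ratio to either the intervention group or control group".

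The arms then differ in how care is delivered. Under the personalized lifestyle intervention: "The first and main component of the intervention involves three personal sessions with a certified lifestyle coach". The coach also agrees the goals and hands out the vouchers. Under the control group: "The control group receives general health advice through a similar binder". No coach is involved there.

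The process evaluation section shows that there are several coaches with several patients each: "We aim to code at least four sessions with different patients of each lifestyle coach (weighed for total number of patients counselled". It also says that coaches keep structured logs of their sessions.

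The effectiveness analysis section states the model. Its random effects are: "Models will use a random intercept (individuals) and, if likelihood ratio testing suggests better fit, random slopes (time". Group, time and their interaction are fixed effects, with "study site and diagnostic group (SCD or MCI) as fixed covariates". No coach term or cluster-robust variance is named. The sample size section takes one LIBRA2 point as the target, which "would translate into a Cohen’s d = 0.35", and describes no allowance for clustering.

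**The concern.** This is a partially nested design: participants are randomized individually, but one arm is then grouped by coach. If some coaches achieve more change than others, the 12-month changes of participants who share a coach are correlated. A model that treats them as independent overstates the information in the intervention arm.

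The stated terms do not absorb this correlation. The site effect is common to both arms and both time points, whereas a coach effect acts on change in the intervention arm only. A participant random slope describes variation between participants but remains independent from one participant to the next.

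At stake is the precision claimed for the primary effect. The discussion and conclusions look towards use in hospitals across the Netherlands, that is, by other coaches. For that purpose, variation between coaches belongs in the error of the estimate.

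**Working it through.** **The plan's own figure.** For d = 0.35, 80% power and two-sided 5%, the normal approximation gives 129 per group and the t-test 130. An unrounded d of 0.345 gives 133 with the t-test. Then 133/0.9 = 147.8, so 148 per group and 296 in total, rounded to 300. The figure is reproduced on the basis of independent participants, with no design effect.

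**Inputs.** From the article: 133 analysed per arm and d = 0.35. Assumed, because the article does not give them: K coaches with equal caseloads (4 to 20), and a coach ICC on 12-month change (0.01 to 0.05).

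**Formulas.**
- Caseload m = 133/K.
- Design effect in the intervention arm: DE = 1 + (m − 1) × ICC. In the control arm it is 1.
- True SE / model SE = √((1 + DE)/2).
- Actual type I error = 2 × (1 − Φ(1.96/ratio)).
- Power once clustering is counted = Φ(0.35/√((1 + DE)/133) − 1.96).

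**Example, K = 6 and ICC = 0.02.** m = 22.2; DE = 1 + 21.2 × 0.02 = 1.42; ratio = √(2.42/2) = 1.10; type I error 7.5%; power 73.7%.

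| Coaches | ICC | DE | SE ratio | Type I error | Power at d = 0.35 |
|---|---|---|---|---|---|
| any | 0 | 1.00 | 1.00 | 5.0% | 81.4% |
| 4 | 0.01 | 1.32 | 1.08 | 6.9% | 75.4% |
| 4 | 0.02 | 1.65 | 1.15 | 8.8% | 69.9% |
| 4 | 0.05 | 2.61 | 1.34 | 14.5% | 56.5% |
| 6 | 0.01 | 1.21 | 1.05 | 6.2% | 77.5% |
| 6 | 0.02 | 1.42 | 1.10 | 7.5% | 73.7% |
| 6 | 0.05 | 2.06 | 1.24 | 11.3% | 63.6% |
| 10 | 0.01 | 1.12 | 1.03 | 5.7% | 79.1% |
| 10 | 0.05 | 1.62 | 1.14 | 8.7% | 70.4% |
| 20 | 0.01 | 1.06 | 1.01 | 5.3% | 80.4% |
| 20 | 0.05 | 1.28 | 1.07 | 6.7% | 76.2% |

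A simulation of change scores (8,000 runs per setting) agrees. For 4 coaches and ICC 0.05 it gives a ratio of 1.34 and a type I error of 14.6%; for 10 coaches and ICC 0.05, 1.15 and 8.8%.

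**The power column is one scenario.** It makes no use of the baseline, which the planned model includes. Let ρ be the baseline to follow-up correlation (assumed; not in the article) and s the coach variance as a fraction of the follow-up variance. The variance of the difference in change is then (4(1 − ρ) + m × s)/133. With 6 coaches:
- ρ = 0.7: power is about 88% for s = 0.02 and 76% for s = 0.05.
- ρ = 0.5: 73% and 63%.

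A higher ρ restores power but does not remove the understatement of the standard error.

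**Cost of allowing for coaches.** Satterthwaite df = (DE + 1)²/(DE²/(K − 1) + 1/132).
- 6 coaches, ICC 0.02: 2.42²/(1.42²/5 + 1/132) = 14.3, so t = 2.14. Interval width relative to the present model: 1.10 × 2.14/1.96 = 1.20.
- 4 coaches, ICC 0.05: 3.61²/(2.61²/3 + 1/132) = 5.7, so t is about 2.48. Relative width: 1.34 × 2.48/1.96 = 1.70.

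**The case against.** The strongest reply is that the harm is conditional. A reader might infer that the standard error is too small as a matter of fact. The article does not support that: it gives neither an ICC nor a number of coaches, and with 20 coaches and an ICC of 0.01 the error is trivial. The outcome also points towards a low ICC. LIBRA2 sums yes/no factors, several of which are not on the article's own list of those modifiable within a year, and contact amounts to three sessions. This stands. It bears on the size and does not show that the ICC is zero.

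A reader might also infer that the protocol expects coaches to differ, because sessions from every coach are scored for motivational-interviewing fidelity. The text does not say so. The stated purpose is a competency score for fidelity across the trial.

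The type I error needs care as well. If the intervention changes nothing for anyone, there are no coach effects and the test keeps its level. Inflation arises when coach effects vary around a zero mean and the coaches are regarded as a sample of possible coaches. Inference limited to the trial's own coaches is a legitimate, narrower aim, and the stated model would serve it.

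Finally, this is a condensed article. The number of coaches, a sample size allowance or a coach-level sensitivity analysis may be in documents not shown, so their absence here is not held against the plan. The random-effects structure is different, because the article states it.

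**Conclusion.** The point holds in conditional form. The nesting of one arm and the participant-only random effects can both be read in the article. If the coach ICC is above zero, the stated model gives a standard error that is too small for inference beyond these coaches. Under the assumed 4 to 20 coaches and ICC of 0.01 to 0.05, with 133 analysed per arm, the true standard error is 1.01 to 1.34 times the model's. Type I error is 5.3% to 14.5%, given coach effects around a zero mean. The upper end needs both few coaches and the highest ICC tried. No single power loss can be stated, because it depends on the unreported baseline correlation. This should be settled before analysis, but it does not invalidate the design.

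**What to change.** Prespecify a partially nested mixed model: the present model plus a random coach effect on the 12-month outcome in the intervention arm only, with each control treated as a singleton. Fit it by REML with Satterthwaite or Kenward-Roger degrees of freedom. Present it at least as a sensitivity analysis beside the primary model. Take coach identity from the session logs, report the number of coaches and the coach ICC, and limit the conclusion to the trial's own coaches if the two analyses disagree.

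This changes only the analysis text and needs no extra participants or visits, provided that the logs identify the coach. The statistical cost is real. Intervals may be clearly wider: about 20% for 6 coaches and an ICC of 0.02, and about 70% for 4 coaches and an ICC of 0.05. With few coaches the coach variance is poorly estimated, which is the main argument for keeping this as a sensitivity analysis rather than replacing the primary model.
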